## Discussion

Although it is generally accepted that RCTs provide the highest level of evidence in health care research, randomization in the current study is neither feasible nor acceptable to study participants [24]. Moreover, RCTs are not always the best study design for evaluation of the implementation of complex interventions, which typically include multiple components, target multiple outcomes, or aim to achieve outcomes that are difficult to influence [91]. Using a quasi-experimental design, this study will fill an important gap in the evidence base for smoking cessation in hospitalized patients, as the effectiveness of brief bedside counseling combined with sustained relapse prevention is unclear. The two studies that combined brief inpatient counseling with sustained relapse prevention were limited by insufficient power [92], lack of data on the extent to which the relapse prevention component was implemented [92], and failure to include pharmacotherapy as part of intervention [93].

Limitations of the proposed study design deserve comment. Pre-post changes in outcome may be attributable to 'history' (the influence of events during the study that affect the study outcomes) or 'maturation' (the change of staff performance during the study related to the evolution of clinical skills) [25]. Potential Hawthorne effects should be minimized by employing a sufficiently long intervention period (six months). We will check for any time-related changes in cessation counseling or patients' intention to quit during the enrollment period in each hospital. This will allow us to closely monitor any secular trends (*e.g*., release of new smoking cessation aids, changes in hospital policies) that might impact upon delivery of cessation counseling or cessation outcomes. In addition, we will account for any confounder variables that show significant imbalances between baseline and intervention periods in multivariable analyses.

This project directly addresses one of the key recommendations to emerge from the VA Large Health Study: 'We must find ways to identify and target those ready to quit using tobacco so that limited resources have greater effect [2].' If the study intervention is shown to be effective, it will provide insights on how the CCM can be applied to promote implementation of smoking cessation guidelines in hospitals, and more generally, how to improve the continuity of preventive services as patients make the transition from the hospital to outpatient setting. The results of this research can be used by clinicians, quality managers, and VA decision makers to improve the quality of smoking cessation services (above and beyond 'ask' and 'advise' performance measures) [94,95]. If the study intervention leads to a 7% increase in quit rates, this would result in 7,000 new non-smokers annually if implemented system-wide (of the approximately 100,000 smokers who are admitted to VA hospitals annually).

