## Methods

### Study design

This study is a before-after trial (with each site serving as its own control) in smokers who are hospitalized on the medical wards of four VA hospitals (Figure 1). After a six-month baseline period of enrollment, the research team will conduct focus groups of clinical staff at each site, adapt the strategy for guideline implementation, and train clinical staff at each site. A new cohort of study patients will be enrolled over the subsequent six-month intervention period. Staggering the timing of intervention across sites will allow us to collect concurrent control data for three of the four study sites during intervention; this will enable detection of system-wide trends in the delivery of cessation counseling, measurement reactivity, and other potential confounding factors within each period (except the final period)[24,25]. We considered cluster randomization by hospital, but the cost of conducting such a trial was not feasible due to budgetary constraints (as at least four sites per comparison group are typically required) [26].

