### Self-management support

Patient self-management support will consist of brief inpatient counseling, pharmacotherapy, and follow-up telephone counseling after discharge. Because of its convenience, telephone counseling has emerged as a popular and effective alternative for delivery of self-management support [42-45]. Moreover, the importance of sustained relapse prevention has been demonstrated in systematic reviews to be an essential component of smoking cessation [11,17,46]. In a recent randomized controlled trial (RCT) of comprehensive telephone care versus routine care in outpatient VA smokers, telephone care resulted in a higher rate of six-month prolonged smoking abstinence at 12-month follow-up (13 versus 4%, p < 0.001) and 30-day abstinence from smoking (19% versus 13%, p = 0.028) [47]. The linkage of patients to community resources such as tobacco quit lines has also been advocated as a sustainable strategy for providing in-depth cessation counseling in busy practice settings [29].

The goals of brief inpatient counseling are to assess patients' willingness to quit, motivate patients to abstain from smoking during and after hospitalization, and assist smokers in formulating a plan for continued abstinence after discharge within five to ten minutes. At admission (or as soon as the patient's acute medical condition has stabilized), staff nurses will be trained to perform the 'five A's' of smoking cessation counseling (ask, advise, assess, assist, and arrange follow-up) [48], to assist patients in moving toward change, and to recognize and manage resistance to behavior change [38,39]. Staff nurses will also be instructed in how to personalize the counseling for patients' admission diagnoses and smoking-related comorbidities, as smokers are more likely to quit if they perceive that they are susceptible to the harmful effects of smoking and perceive greater benefits of quitting) [49,50]. In addition, staff nurses will assess interest in receiving pharmacotherapy to help relieve nicotine withdrawal symptoms.

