### Patient-level data

After obtaining informed consent, the RA will perform a structured interview in current smokers to obtain more detailed information on smoking history (pack-years, number of quit attempts more than one day), other tobacco use (*e.g*., spit tobacco), alcohol use, overall health status, smoking-related medical comorbidities, readiness to quit smoking [23], level of tobacco addiction [71], perceived likelihood of staying off cigarettes after hospital discharge [72], and social support for quitting [6].

Just prior to discharge, the RA will ask eligible smokers whether they abstained from cigarettes during hospitalization, and whether or not the hospital staff had performed recommended smoking cessation counseling during the hospital stay. Patients will also be asked to specify whether they had received these services from their nurse, physician, or other clinician (*e.g*., respiratory therapist) [73]. Patient recall of advice to quit smoking has been shown to be reasonably accurate in assessing performance of guideline-recommended actions in clinical practice (sensitivity 92%, specificity 82% for advice to quit) [74].

At three- and six-month follow-up, research interviewers will contact patients by telephone about their smoking over seven days and 30 days prior to the interview (seven-day and 30-day, PPA), any quit attempts (>24 hours) since hospital discharge, and stage of change. At each follow-up, we will also determine prolonged abstinence (after a one-month grace period). All follow-up interviewers will be blinded to treatment assignment. Patients who report abstinence at six-month follow-up will be mailed a collection kit for salivary cotinine determination (with a follow-up telephone reminder to return the sample). A cutoff of 20 ng/ml will be used to determine abstinence, as this threshold is associated with high sensitivity and specificity (>90%) [75]. To calculate the biochemically confirmed six-month quit rate, we will adjust the seven-day PPA for the results of the cotinine analysis.

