### Sample size calculations

Based on the volume of admissions at each study hospital, we plan to screen 7,548 potential subjects who are hospitalized on medical wards for greater than 24 hours during the enrollment period at the four sites. Based on chart review, we estimated smoking prevalence at each site (weighted average = 23%, range 17 to 32%), and determined that approximately 80% of identified smokers will be eligible to participate in the proposed trial. Assuming that 84% of eligible patients consent to participate (based on a recent VA smoking cessation study [47]), we would expect 1,000 subjects to enroll in the study (500 baseline, 500 intervention). Pooling the control group data from studies of general medical inpatients, we estimate a 12% quit rate at six-months (seven-day PPA). Thus, a study sample of 1,000 patients will have 83% power to detect a seven percentage-point difference between periods in six-month quit rates. This effect estimate is consistent with that observed in prior hospital intervention trials that employed a sustained relapse prevention component [16,20,21]. Based on chart reviews at two study sites, we estimate that 12 and 13% of inpatients during the baseline period will be referred for cessation counseling and will receive recommended pharmacotherapy, respectively. The projected study sample will have 81 and 83% power to detect a seven percentage-point difference in these process measures, respectively. These power calculations are based on a hierarchical linear model, with nurse treated as a random factor (and patient outcomes are clustered within nurse); intracluster correlation (ICC) was estimated to be 0.05 for assistance in quitting (which includes offering of pharmacotherapy and arranging follow-up), and 0.01 for abstinence, based on data from the AHRQ Smoking Cessation Guideline Evaluation Trial [77].

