### Statistical analysis

The primary clinical endpoint of this analysis is seven-day PPA at three and six months. The primary process of care endpoints are referral of patients to telephone counseling (or other outpatient cessation counseling) and prescription of recommended pharmacotherapy for smoking cessation. To evaluate the relationship between the intervention and these outcomes, we will use hierarchical logistic regression to adjust for differences in potentially confounding patient and nurse characteristics between the baseline and intervention period cohorts. In these analyses, each patient will be nested within his/her admitting nurse, who will have primary responsibility for providing brief cessation counseling. To compare how the two arms differ in time to first relapse after hospital discharge, we will use Cox proportional-hazards survival analysis methods with time to relapse as the outcome [83]; in this analysis, intra-nurse correlation will be accounted for by using the robust sandwich estimator [84].

To evaluate the hypothesis that staff nurses will have improved decisional balance scores and higher ratings of self-efficacy in providing cessation counseling as a result of the intervention, we will compare values of these measures obtained at the end of the intervention period to pre-intervention values using a repeated measures ANOVA with site included as a covariate (or a site-stratified Wilcoxon signed-rank test, if the data are skewed or heavy-tailed). To determine whether the intervention effect (if any) is modified by nurses' perceptions of their work, we will check the interaction between treatment and nurse ratings of professional status and adequacy of staffing.

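### Adjusting only for confounders that differ significantly between the two periods is a poor rule for a non-randomised before-after comparison; a fixed prognostic set should replace it

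*Protocol article*

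**What the plan says.** The Study design section describes the trial thus: "This study is a before-after trial (with each site serving as its own control". The two cohorts are different patients enrolled in different six-month periods. Staggered starts give concurrent control data in all but the final period.

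Two places deal with adjustment. The Statistical analysis section says hierarchical logistic regression will "adjust for differences in potentially confounding patient and nurse characteristics between the baseline and intervention period cohorts". The Discussion, on limitations, gives the criterion: "we will account for any confounder variables that show significant imbalances between baseline and intervention periods in multivariable analyses". Neither names a covariate set.

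The Patient-level data section lists what the research assistant (RA) records after consent. Beside smoking history, alcohol use and comorbidities, the list includes "readiness to quit smoking [23], level of tobacco addiction [71], perceived likelihood of staying off cigarettes after hospital discharge [72". On the timing of counseling, the Self-management support section says: "At admission (or as soon as the patient's acute medical condition has stabilized), staff nurses will be trained to perform" the five A's. No section says whether the RA interview comes before or after that counseling.

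**The concern.** Without randomisation, covariate adjustment is a main protection against a change in case mix between periods. Bias from a confounder depends on two things: how far it differs between periods, and how strongly it predicts quitting. A significance test between periods looks only at the first, and its answer depends on sample size. A strong predictor with a moderate imbalance is dropped, while a weak one with a larger imbalance is kept. The rule also makes the primary model depend on the data.

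A second issue is conditional. The rule does not exclude variables that the intervention may itself change. If the RA interview follows bedside counseling, readiness to quit and perceived likelihood of abstinence are partly results of the intervention, and a significant difference in them could be its effect. Nurse attitudes and self-efficacy after training are intervention targets by Hypothesis 2.

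**Working it through.** **Inputs from the protocol (Sample size calculations; Statistical analysis).** "we would expect 1,000 subjects to enroll in the study (500 baseline, 500 intervention"; "we estimate a 12% quit rate at six-months (seven-day PPA"; two-sided 0.05; intracluster correlation 0.01 for abstinence. Cluster size per nurse is not stated.

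**1. The plan's own figure.** It states "83% power to detect a seven percentage-point difference between periods in six-month quit rates", that is, 12% v 19%. Without clustering, the pooled rate is 0.155 and

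power = Φ{[0.07 − 1.96√(2×0.155×0.845/500)] / √[(0.12×0.88 + 0.19×0.81)/500]} = 86.5%.

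With an assumed 10 patients per nurse, the design effect is 1 + 9×0.01 = 1.09, effective n is 500/1.09 = 459, and power is 83.5%. With 15 per nurse it is 81.8%. The stated figure is reproduced, and this point does not alter it.

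**2. Largest imbalance that escapes the screen.** For a binary confounder of 50% prevalence (assumed), this is 1.96 × √(2×0.25/500) = 0.062, or 6.2 points.

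**3. Chance that a true imbalance d is flagged at p<0.05.** For d = 0.05: Φ{(0.05 − 0.062)/√(2×0.475×0.525/500)} = Φ(−0.38) = 35%.

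| True imbalance (points) | 3 | 4 | 5 | 6 | 8 | 10 |
|---|---|---|---|---|---|---|
| Flagged | 16% | 24% | 35% | 48% | 72% | 89% |

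**4. Effect of an imbalance left in.** Shift in the quit-rate difference = imbalance × difference in quit rate between confounder levels. With overall quitting at 12% and half of patients at each level, assumed odds ratios of 2, 3 and 4 give level-specific rates of 8.4% v 15.6%, 6.6% v 17.4% and 5.4% v 18.6%.

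| Odds ratio for quitting | 3-point imbalance | 5-point | 6-point |
|---|---|---|---|
| 2 | 0.21 | 0.36 | 0.43 |
| 3 | 0.33 | 0.54 | 0.65 |
| 4 | 0.40 | 0.66 | 0.79 |

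These are percentage points for an imbalance of that size present in the data. The average over repeated trials is smaller, because the larger sample imbalances are the ones flagged. For a true 6-point imbalance, the mean sample imbalance among trials that miss it is 0.06 − 0.0316×φ(0.063)/Φ(0.063) = 0.036.

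**5. Several confounders, true odds ratio 1.** Each scenario used 3,000 simulated trials of 500 per period with no nurse clustering. All imbalances ran in the same direction, which is unfavourable because opposite ones would partly cancel. Each cell gives mean odds ratio and type I error.

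| Scenario | Unadjusted | Significance screen | All entered |
|---|---|---|---|
| 4 confounders, OR 2, 3 points | 1.079; 6.7% | 1.045; 5.0% | 0.998; 4.4% |
| 4, OR 2, 5 points | 1.138; 11.3% | 1.052; 6.1% | 0.999; 5.5% |
| 6, OR 2, 4 points | 1.163; 12.8% | 1.076; 6.3% | 0.998; 4.7% |
| 6, OR 1.7, 5 points | 1.160; 13.2% | 1.060; 6.6% | 0.997; 5.6% |

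Simulation error on a 5% rate is √(0.05×0.95/3000) = 0.4 points.

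**6. Readiness, only if counseling came first.** Suppose counseling raised readiness by 10 points from 50% before it was measured, readiness has an odds ratio of 2 to 3 for quitting, and the total effect is 12% v 19%. Readiness is then flagged in about 90% of trials. Under the screen, the mean odds ratio falls from about 1.7 to 1.58–1.62 and power from about 86% to 71–76%. With a 5-point rise it is flagged in about 35% of trials and the mean odds ratio is about 1.70, almost unchanged. If readiness is measured before counseling, none of this arises.

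**The case against.** The strongest defence is that the screen appears in one Discussion sentence, while the Statistical analysis section promises adjustment with no significance condition, and a detailed covariate list may sit in an analysis plan that is not shown. The absence of a list is indeed no fault. The objection, however, is to a criterion the protocol states, and the Statistical analysis wording is compatible with it and does not override it.

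The size is also modest. It rests on assumed prevalences and odds ratios, a single missed confounder costs less than 1 point in the ranges tried, and the screen removes much of the bias that no adjustment would leave. All of that stands.

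A reader might infer something stronger: that the rule will draw readiness into the model after counseling has changed it, and so adjust away part of the effect. The documents do not support this. Counseling takes place at admission or once the patient is stable, the interview follows consent, and their order is not fixed. Excluding stays under 24 hours does not settle it. Readiness is not named as a covariate, and the rule speaks of confounders. Nurse attitudes and self-efficacy appear as outcomes with their own analysis. Because patients enroll whatever their willingness to quit, the cohorts may truly differ in readiness. Measured before counseling, it is a legitimate confounder, and barring it outright could leave real confounding in place.

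**Conclusion.** The point holds as a criticism of the stated selection rule. With 500 per period, a 50%-prevalence confounder truly differing by 3 to 6 points is missed more often than not. An imbalance of that size left in the data moves the quit-rate difference by roughly 0.2 to 0.8 points per confounder, for odds ratios of 2 to 4. With four to six such confounders all leaning one way, the screen leaves a spurious odds ratio of about 1.05 to 1.08, where entering all of them leaves about 1.00. The confounder prevalences, odds ratios and imbalances are assumptions, and nurse clustering was ignored in the simulations. The sample-size statement is unaffected.

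Over-adjustment for readiness or nurse attitudes is a possibility that the rule does not guard against. It is not an established consequence. This should be changed, but it does not invalidate the design.

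**What to change.** Replace the Discussion rule, and align the Statistical analysis section, with a pre-specified covariate set entered regardless of p-value. Draw it from variables already available that the intervention cannot alter: hospital, age, sex, pack-years, level of tobacco addiction, prior quit attempts, smoking-related comorbidity and alcohol use.

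State that readiness to quit and perceived likelihood of abstinence do not enter the primary model merely because they differ significantly between periods. Use readiness as a covariate only where it was measured before bedside counseling, which requires recording the order of the two. Otherwise show the model with and without it as a sensitivity analysis. Apply the same principle to nurse attitudes and self-efficacy measured after training.

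The cost is a change of analysis wording, a few more model parameters and one extra sensitivity analysis. Where readiness was measured too late to be used, a true prior difference in it stays uncorrected in the primary model, which is why the sensitivity analysis is needed.

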### Ethics

This protocol was approved by the Institutional Review Board at the University of Iowa on 12 November 2008 (IRB protocol 200805711).
